### Study purpose and objectives

The purposes of this study are to evaluate early and delayed effects of transcranial light-emitting diode (LED) therapy (TCLT) and determine whether this therapy is effective for the cognitive rehabilitation of DAI patients after TBI.

### Primary outcome measures

The primary hypothesis is that there will be evidence of improvement in functional outcome measured by the Glasgow Outcome Scale Extended (GOSE) after stimulation in comparison to the placebo group at 3 months.

### Secondary outcome measures

Improvement effects of TCLT in follow-up images will be measured by the Marshall computed tomography scale and Adams grading scale for DAI. The hemodynamic improvement effect of TCLT will be measured by transcranial Doppler (systolic and diastolic velocities of the left middle cerebral and basilar arteries, and pulsatility index and resistance index values).

## Methods/design

### Study design

This study is a sham-controlled, randomized, single-center trial where data will be collected from patients admitted in the emergency service of University of São Paulo General Hospital, São Paulo, Brazil. The recruitment period started in October 2017, and the estimated data collection conclusion is October 2018.

The present trial will respect CONSORT (Consolidated Standards of Reporting Trials) guidelines and SPIRIT (Standard Protocol Items: Recommendations for Interventional Trials) guidelines as shown in Fig. 1 and Additional file 1, respectively.

**Fig. 1 Fig1:**
[figure not shown]
Template of content for the schedule of enrollment, interventions, and assessments from the LED TBI protocol. Baseline variables are evaluated before the intervention. The primary variable is evaluated 3 months after the intervention, and the secondary variables are evaluated during the whole period of this study. *GOSE* Glasgow Outcome Scale Extended

### Sampling

The eligibility criteria will include adult patients between 18 and 60 years who are victims of a severe (Glasgow Coma Scale ≤8) acute (hospital admission within less than 8 h from trauma) TBI and present with the DAI diagnosis. Patients younger than 18 years old will be excluded due to the known different physiopathology typical of this age. We excluded patients older than 60 because different studies revealed that these patients had a significantly worse outcome after TBI. Six months after severe head injury, 92% were dead, vegetative, or severely disabled. Four class I studies demonstrated a mortality of >75% in severely brain-injured patients older than 60. The critical age threshold for worsening prognosis appears to be above 60 in a review of class I and II studies [43].

DAI diagnosis is histopathological. It can be clinically defined by coma lasting 6 h or more after TBI, excluding cases of swelling or ischemic brain lesions [44, 45]. Focal brain injury may produce mass effects from hemorrhagic contusion or hematoma, which can induce herniation and brain stem compression, and the resultant may be coma, which is not usually immediate but develops in a secondary fashion. Otherwise, DAI can be a sole source of post-traumatic coma in the absence of mass lesions [45]. MRI will be performed in all patients for documentation. However, MRI cannot demonstrate DAI lesions in up to 10% of patients. Therefore, patients with Glasgow Coma Scale (GCS) ≤8 lasting more than 6 h without MRI or with normal CT or normal MRI will also be diagnosed as having DAI, if no other reasons justify the coma status [44–46]. Patients will be considered to have awakened from coma when they score 6 points in the best motor response in the GCS, consequently not being included in this protocol.

In summary, the inclusion criteria will be:Coma lasting more than 6 h without sedationCT scan without focal surgical lesions (Marshall I and II) and no signs of intracranial hypertensionTranscranial Doppler and optic nerve sheath US with no signs of intracranial hypertensionAdmission within less than 8 h of trauma

The exclusion criteria will be:History of drug or narcotic abuseEmergence of surgical lesions or signs of intracranial hypertension in follow-up CTsTranscranial Doppler or optic nerve sheath US presenting signs of intracranial hypertensionPsychiatric disordersInjury severity score ≥3, according to the Abbreviated Injury Scale [47]Bilateral fixed and dilated pupils

The optic nerve sheath is contiguous with the subarachnoid space. Thus, an increase in ICP results in a corresponding increase in the optic nerve sheath diameter. The cutoff point which will be considered intracranial hypertension in this protocol is ≥5 mm [48].

The transcranial Doppler can estimate ICP through a formula, calculated using the mean systemic arterial blood pressure (ABP), the arterial resistivity index (RI), and the mean flow velocity of the cerebral arteries (MFV): ABP × RI/MFV [49].

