### Severe TBI evaluation and management at University of São Paulo General Hospital

At University of São Paulo General Hospital, all severe TBI patients are managed in an intensive care unit. An ICP monitoring catheter is inserted in patients who present with the criteria for ICP monitoring [50]:

GCS ≤8 and:▪ Marshall ≥2 head CT scan or▪ Normal head CT scan and at least two of the following three criteria:PAS ≤90 mmHgAge >40Pathological posture (decerebration or decortication)

The decision for catheter insertion is made by the on-call attending neurosurgeon. Patients in whom the catheter cannot be inserted for any reason are evaluated by non-invasive strategies (optic nerve sheath ultrasonography or transcranial Doppler) for ICP monitoring and CT scan. In our center, all TBI patients are submitted to head CT scans at admission, within 6 h after trauma, on the third and the fifth day after trauma, or before these times if they present any neurological deterioration (which is commonly defined as a decrease of two or more points in the motor component of the Glasgow Coma Scale) [51]. When patients need to be hospitalized for longer than 5 days, the decision for the following head CT scans is individualized. All TBI patients in coma are evaluated with electroencephalogram (EEG) for seizure diagnosis in the intensive care unit (ICU).

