### Tolerability and safety

All patients will be evaluated after each session. If a major side effect is noticed, medical assistance will be provided for the patient and further examination will be done as necessary. This fact will be written down and discussed to avoid future occurrences. Depending on the case, exclusion of the patient will be considered.

There are no studies with photobiomodulation (PBM) for severe TBI patients in the acute stage of trauma. Considering that fact, some safety precautions will be taken. There are no papers studying the possible effect of increasing the ICP due to PBM. But some chronic-stage studies [52] noticed a blood flow increase. The possible ICP increase due to that will be monitored by ICP catheter insertion or non-invasive methods (when catheter insertion cannot be performed for any reason). Because of the improvement effect in chronic TBI patients, the authors do not believe that this intervention could be harmful. ICP monitoring will add safety to this study. If elevation of ICP happens, the authors will stop the session and observe if intervention for ICP control is required. The patient will be evaluated in the following session, and if elevation happens again, the patient will be excluded.

Another concern would be a possible deleterious effect produced by the heat generated by the helmet in acute-stage TBI patients. Some studies showed an insignificant cortical temperature increase [52, 53]. Our device has already been considered safe in this regard; in addition, the protocol includes monitoring the head skin and global temperature of the patient during the sessions. If there is harmful elevation of skin temperature in the area of stimulation, the session will be interrupted and the patient will be reevaluated. If this effect is noticed in the following session, exclusion of the patient will be considered for safety.

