### Cerebral blood flow evaluation

#### Transcranial Doppler

All patients will be evaluated by transcranial Doppler before the first stimulation and after the last one. Evaluation will be done by a doctor expert in transcranial Doppler who will not be aware of the patient’s group (intervention vs sham). The transcranial Doppler parameters of evaluation include the following: blood flow velocities (systolic and diastolic) of the bilateral middle cerebral arteries as well as the basilar artery. The device that will be used for measuring is a transcranial Doppler ultrasound (LOGIQ; GE Healthcare Systems, Wauwatosa, WI, USA, 2012) with a 2-MHz transducer. The mean flow velocity (cm/s) will be obtained every second (sampling rate of 1 Hz) and saved for analysis. The three best measures of the systolic velocity, diastolic velocity, pulsatility index, and resistance index will be selected to calculate the mean values [52].

Evaluation with the transcranial Doppler will be performed by one expert doctor only to maintain a uniform measurement of TBI patients.

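### The printed Doppler formula for ICP (ABP × RI/MFV) does not yield a pressure and has no cut-off, so the Doppler criterion for intracranial hypertension cannot be applied as written

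*Protocol article*

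**What the plan says.** All references are to the protocol article.

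- **Sampling, formula.** "The transcranial Doppler can estimate ICP through a formula, calculated using the mean systemic arterial blood pressure (ABP"), with the other terms given as "the arterial resistivity index (RI), and the mean flow velocity of the cerebral arteries (MFV): ABP × RI/MFV". No scale factor, intercept, output unit or cut-off follows. The sentences just before it do set a cut-off for optic nerve sheath diameter: "The cutoff point which will be considered intracranial hypertension in this protocol is ≥5 mm".
- **Sampling, criteria.** Inclusion needs both Doppler and sheath ultrasound free of signs of intracranial hypertension, and a CT without such signs. Signs on either Doppler or sheath ultrasound exclude the patient.
- **Transcranial Doppler.** The velocity unit is fixed here: "The mean flow velocity (cm/s) will be obtained every second (sampling rate of 1 Hz").
- **Severe TBI evaluation and management.** Patients in whom a catheter cannot be placed are "evaluated by non-invasive strategies (optic nerve sheath ultrasonography or transcranial Doppler) for ICP monitoring and CT scan".
- **Tolerability and safety.** The feared mechanism is flow: "But some chronic-stage studies [52] noticed a blood flow increase". The safeguard is monitoring: "The possible ICP increase due to that will be monitored by ICP catheter insertion or non-invasive methods". The session rule is: "If elevation of ICP happens, the authors will stop the session and observe if intervention for ICP control is required". No numeric threshold is attached to that rule, and the Doppler formula is not cited there.

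**The concern.** The formula is the only text that says how a Doppler examination bears on ICP, and it stands directly after the eligibility criteria that use Doppler signs of intracranial hypertension. If its output is not a pressure and has no cut-off on any other scale, an examiner has nothing to compare it with. Compared with a pressure threshold in mmHg, it would look normal in practically everyone.

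The sign also matters. The hazard described under Tolerability and safety is an ICP rise brought about by increased blood flow. Flow velocity is in the denominator, so the first consequence of more flow, other things equal, is a lower estimate.

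At stake are who is enrolled and, for patients without a catheter, what counts as an ICP elevation. By the protocol's own account there are no earlier studies of photobiomodulation in acute severe TBI, and ICP monitoring is offered as the added safety measure.

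**Working it through.** The protocol states no numerical result for this formula, so there is no figure to reproduce. The check covers units, size and direction.

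**Inputs**
- Expression: ABP × RI/MFV (Sampling).
- MFV in cm/s (Transcranial Doppler).
- ABP taken in mmHg, the unit the article uses for blood pressure elsewhere.
- RI taken as a ratio of velocities, (PSV − EDV)/PSV, where PSV and EDV are the systolic and diastolic velocities. It therefore has no unit. This is an assumption, because the article does not define RI.
- Input ranges are assumed, because the article gives none: ABP 70-110 mmHg, RI 0.5-0.9, MFV 25-70 cm/s. A wider set is ABP 65-120, RI 0.45-0.90, MFV 20-100.

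**1. Units.** mmHg × 1 ÷ (cm/s) = mmHg·s/cm. The number also depends on the velocity unit: 90 × 0.6/50 = 1.08 with MFV in cm/s, but 90 × 0.6/0.50 = 108 for the same patient in m/s. A pressure would not change in that way.

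**2. Size**
- Lowest in the assumed range: 70 × 0.5/70 = 0.50.
- Mid-range example: 90 × 0.6/50 = 1.08.
- Highest: 110 × 0.9/25 = 3.96.
- Wider range: 65 × 0.45/100 = 0.29, up to 120 × 0.90/20 = 5.4.
- For the expression to return 20 (an illustrative pressure in mmHg, not a protocol figure) at ABP 90 and RI 0.6, MFV would have to be 90 × 0.6/20 = 2.7 cm/s. Even at RI 1.0 it would be 90 × 1.0/20 = 4.5 cm/s. Both are far below the assumed velocities.

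**3. Direction.** The new value divided by the old is (1 + change in ABP)(1 + change in RI)/(1 + change in MFV), with changes as proportions. With ABP and RI unchanged:
- MFV +20%: 1/1.2 = 0.83, a fall of 17%.
- MFV +30%: 1/1.3 = 0.77, a fall of 23%.

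**4. Can it rise?** Yes. Take ABP 90 and the approximation MFV = (PSV + 2 × EDV)/3 (assumed):

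| PSV/EDV (cm/s) | RI | MFV (cm/s) | Value |
|---|---|---|---|
| 90/38 | 0.58 | 55 | 0.94 |
| 90/25 | 0.72 | 47 | 1.39 |
| 90/15 | 0.83 | 40 | 1.88 |
| 110/35 | 0.68 | 60 | 1.02 |

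In the second and third rows diastolic velocity falls, RI rises and MFV falls, so the value climbs. In the last row MFV is higher than in the first, yet the value is 9% higher (1.02/0.94), because RI rose proportionally more.

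**5. Where it bears on the trial.** Marshall I and II are eligible. The catheter criteria list Marshall 2 or above, or a normal CT with at least two of three further features. A Marshall I patient without two of those features is eligible but not listed for a catheter. The word *or* in the non-invasive strategies then permits Doppler in place of sheath ultrasound.

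**The case against.** Four points can be made on the other side.

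**The index can move the right way.** A reader might infer that the formula cannot flag a flow-driven ICP rise at all. The document does not support that. The falls of 17% and 23% hold ABP and RI fixed, whereas a real rise in ICP may change RI or lower velocity, and the value then goes up, as the table shows. This objection stands. What remains is that the direction is adverse when velocity alone rises.

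**The link to the session rule is indirect.** The formula is in Sampling. Tolerability and safety names the catheter first and does not cite the formula. The fallback also includes sheath ultrasound and CT. A reader might infer that sessions are stopped or continued on this number alone, or that the trial would under-report ICP elevations. No section says the former, and no rate of ICP elevation is listed among the outcomes. This also stands. The point reaches the session rule only for patients without a catheter who are followed by Doppler alone, which the text permits but does not prescribe.

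**Eligibility has other protection.** A falsely reassuring Doppler value cannot admit a patient whose CT or sheath measurement is abnormal. That is right, and it limits the harm, but it leaves the Doppler criterion itself without working content.

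**The article is condensed.** A Doppler cut-off may be in the full protocol or in the source cited for the formula, neither of which is at hand, and Doppler signs may be meant more broadly than this one number. For that reason the missing cut-off alone would not be worth raising. The article does, however, print an expression and say it estimates ICP, and as printed it does not.

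**Conclusion.** The point holds in a limited form. As printed, ABP × RI/MFV is not a pressure. Its unit is mmHg·s/cm, and it is about 0.5 to 4 over the assumed inputs (0.3 to 5.4 over the wider set). No cut-off is given on that scale. The unit argument needs no assumed values, only RI as a pure ratio. The size depends on the assumed ranges, but no combination in either set comes near the illustrative 20.

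Two consequences follow from reading the text literally: the Doppler element of the eligibility criteria would never identify intracranial hypertension, and nor would Doppler-only monitoring where no catheter is in place. The adverse direction (MFV +20% gives −17%) is conditional on unchanged ABP and RI.

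The document does not show that the ICP safeguard as a whole fails. The catheter, CT and the sheath cut-off still operate, and the analysis of the primary outcome is unaffected. The error concerns a stated eligibility and safety measure and should be corrected.

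**What to change.** In Sampling, either correct the expression so that it yields a pressure in mmHg, or describe it as an index and give a cut-off on its own scale. State the units of each input in both cases.

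Then reconcile four places: the Doppler criteria and the formula (both in Sampling), the non-invasive strategies (Severe TBI evaluation and management) and the session rule (Tolerability and safety). They should agree on how a Doppler reading counts as intracranial hypertension, and on which of the measures already named decides eligibility and the stopping of a session. Any threshold or clinical rule is for the investigators to set.

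The cost is protocol wording. If patients have already been screened with the printed expression, the investigators should also record how their Doppler readings were judged.

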### Severe TBI evaluation and management at University of São Paulo General Hospital

At University of São Paulo General Hospital, all severe TBI patients are managed in an intensive care unit. An ICP monitoring catheter is inserted in patients who present with the criteria for ICP monitoring [50]:

GCS ≤8 and:▪ Marshall ≥2 head CT scan or▪ Normal head CT scan and at least two of the following three criteria:PAS ≤90 mmHgAge >40Pathological posture (decerebration or decortication)

The decision for catheter insertion is made by the on-call attending neurosurgeon. Patients in whom the catheter cannot be inserted for any reason are evaluated by non-invasive strategies (optic nerve sheath ultrasonography or transcranial Doppler) for ICP monitoring and CT scan. In our center, all TBI patients are submitted to head CT scans at admission, within 6 h after trauma, on the third and the fifth day after trauma, or before these times if they present any neurological deterioration (which is commonly defined as a decrease of two or more points in the motor component of the Glasgow Coma Scale) [51]. When patients need to be hospitalized for longer than 5 days, the decision for the following head CT scans is individualized. All TBI patients in coma are evaluated with electroencephalogram (EEG) for seizure diagnosis in the intensive care unit (ICU).

### Recruitment

A total of 32 patients, of both genders, from 18 to 60 years old who meet the inclusion and exclusion criteria will be evaluated. All eligible recruited patients will be admitted to the Emergency Department of University of São Paulo General Hospital and randomly divided into two groups (active coil LED helmet vs sham). All patients will receive a unique identification number, which will be used along the study to keep the staff blinded.

### Randomization and blinding

The randomization process will be achieved through a computer software, respecting a 1:1 ratio for the 30 patients. The method of randomization used by the computer software is random permuted block sizes of 2. The two groups will be active coil and sham coil. As this is a double-blinded study, neuropsychologists and patients (as well as their relatives) will be blinded to the group assignment. The method of blinding will consist of using an equal helmet for both the intervention and placebo groups. Both helmets will emit a red light, but only the active coil group will receive LED emission (intervention group).

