**Fig. 2 Fig2:**
[figure not shown]
Study protocol flow diagram. Thirty patients who meet the inclusion and exclusion criteria will be recruited from the Emergency Department of University of São Paulo General Hospital. After baseline data collection, GOSE evaluation, transcranial Doppler hemodynamic measures, and CT scan, these patients will be randomized at a 1:1 ratio: active coil group vs sham coil group. They will be submitted to 18 sessions of TCLT three times per week and reevaluated with the aforementioned instruments after 1, 3, and 6 months after trauma

During the TCLT sessions, patients will remain seated in bed with head support and with their eyes protected. Eighteen sessions will be carried out, with a total of 56 applications. The same qualified previously trained therapist will perform all TCLT sessions at the same time of the day.

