### Blinding and allocation concealment committee

In the present study, there is a medical committee who can remove blinding, if something unexpected happens: a major adverse event, patient dropout, etc. The medical committee is not directly related to any patient group.

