### Sample size calculation

The previously published studies about transcranial LED therapy are case reports or case series. Besides, there is no study which evaluated transcranial LED therapy for acute severe TBI patients. Considering these facts, the sample size was calculated based on the primary outcome proportion difference (favorable vs unfavorable) on chi-square with the estimation of effect size (Cohen’s *D*) of 0.5, alpha of 5%, and statistic power of 80%. The final result was 32 patients, who will be divided into two groups (16 patients each).

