Moderate TBI patients were treated with a high-power NIR laser (10–15 W at 810 and 980 nm) through 20 NIR applications over a 2-month period. They showed decreased headache, depression, anxiety, and insomnia, whereas cognition and quality of life improved, accompanied by changes in the SPECT imaging [70].

After 18 TCLT treatments (26 J/cm^2^ per LED cluster head placement red/NIR, 500 mW, 22.2 mW/cm^2^) in left-hemisphere stroke patients with chronic aphasia, resting-state fMRI scans have been obtained and shown significant increases in “naming ability” [10].

The 3-month period was chosen for the primary outcome because it presents an important relationship with the first year’s outcome. The usual result expected for severe TBI patients is about 30% of favorable outcome at 3 months [71]. Considering a strong size effect for the intervention, we expect a treatment effect of 50 percentage points (difference in the favorable-outcome rate of 30% vs 75%).

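### A single published block size of 2 at one centre means that any one known allocation gives away its pair: a vulnerability, not a shown breach

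*Protocol article*

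**What the plan says.** - **Block size.** The section Randomization and blinding says: "The method of randomization used by the computer software is random permuted block sizes of 2". Only one size is named, so this cannot be read as randomly varying sizes.
- **Setting.** Study design says: "This study is a sham-controlled, randomized, single-center trial". No stratification is described, so I take it that one list serves all patients.
- **Unblinding.** The section on the blinding and allocation concealment committee says that "there is a medical committee who can remove blinding, if something unexpected happens: a major adverse event, patient dropout, etc". It adds that the committee stands apart from the patient groups.
- **Who is blinded.** Randomization and blinding names neuropsychologists, patients and relatives. Recruitment says, in general terms, that identification numbers serve to keep staff unaware of the arm. The Transcranial Doppler section blinds the Doppler examiner.
- **Therapist.** The text under Fig. 2 says: "The same qualified previously trained therapist will perform all TCLT sessions at the same time of the day". Whether this person is blinded is not specifically stated.
- **Timing.** Trial status dates the start of recruitment to 10 October 2017. The article appeared on 24 April 2018, so the list was already in use.

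**The concern.** A block of 2 is either active then sham, or sham then active. One member's arm fixes the other's, in both directions. With one list at one centre, enrolment order shows who is paired with whom, and the block size is public.

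Two things would be at stake if an arm leaked. If the partner were not yet enrolled, whoever held the information would know the next allocation before deciding on entry. If the partner were already enrolled, that patient would also be unblinded, possibly before the 3-month GOSE that forms the primary outcome. An unblinding prompted by one patient's dropout could thus expose a second patient who is still under follow-up.

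The trial is small: with 16 per arm, one patient is 1/16 = 6.25 percentage points of the favourable-outcome rate.

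**Working it through.** **1. The plan's own figure.** Sample size calculation gives an effect size "of 0.5, alpha of 5%, and statistic power of 80"%, and a total of 32. Taking 0.5 as the chi-square effect size w, with two-sided alpha:

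N = (1.960 + 0.842)² / 0.5² = 7.849 / 0.25 = 31.4, rounded up to 32 (power 80.7%).

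The stated 32 reproduces. Block size does not enter this formula, so the point below leaves the sample size untouched.

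**2. Certain allocations.** Within a permuted block of size b at 1:1, every allocation after one arm is used up is certain. The expected share is 2/(b + 2).

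**3. Correct guesses by someone who knows all past arms.** For b = 2, the first guess is right with probability 0.5 and the second with probability 1, so the average is (0.5 + 1)/2 = 0.75. For b = 4, the four positions give 0.5, 2/3, 2/3 and 1, so the average is 2.833/4 = 0.708. For b = 6, enumeration of all sequences gives 0.683.

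**4. One unblinded patient.** The chance of naming a given block-mate's arm correctly, by guessing the opposite arm, is (b/2)/(b − 1).

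| Scheme | Certain allocations | Correct guesses, all past arms known | Naming one block-mate |
|---|---|---|---|
| Fixed 2 (plan) | 50% (16 of 32) | 75% (24 of 32) | 100% |
| Fixed 4 | 33.3% (10.7 of 32) | 70.8% | 66.7% |
| Fixed 6 | 25% (8 of 32) | 68.3% | 60% |
| Random mix of 4 and 6 | about 6% (1.8 of 32) | about 69% (22.0 of 32) | not computed |

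The last row comes from 4,000 simulated lists of 32. The guesser is allowed to know that the sizes are 4 and 6 but not their order, which is harsher than keeping the sizes undisclosed.

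**5. List length.** Randomization and blinding speaks of "respecting a 1:1 ratio for the 30 patients", whereas Sample size calculation gives 32. With 30 patients the certain allocations would be 15 of 30, the same 50%. The mismatch is a separate inconsistency.

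**6. How little moves the result.** Discussion expects a "difference in the favorable-outcome rate of 30% vs 75"%. Near those rates, 12/16 against 5/16 gives an uncorrected chi-square of 32 × (12×11 − 4×5)² / (17×15×16×16) = 6.15, p = 0.013. Taking two favourable outcomes away, 10/16 against 5/16 gives 32 × (10×11 − 6×5)² / (15×17×16×16) = 3.14, p = 0.077. This shows how fragile a result from 32 patients is. It is not evidence of bias.

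**The case against.** A reader might infer that concealment is defeated, that GOSE assessors are unblinded, or that enrolment is being steered. The article supports none of these.

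- **Predictability is conditional.** It arises only once an arm is known. The helmets are alike and both emit red light, and nothing shows that recruiters or assessors learn past arms. This stands, and it limits the point to a vulnerability.
- **The therapist is not shown to be unblinded.** The specific list of blinded persons omits the therapist, but the general statement in Recruitment about staff may cover that role. The status is unclear, and no more than that can be said.
- **The committee is separate.** The article does not say that an unblinding result reaches recruiters or assessors. A leak needs someone who is told the arm and also knows the enrolment order. This stands, but the grounds for unblinding remain open-ended.
- **Entry is bounded.** Judgement enters the diagnosis where imaging is normal or MRI is lacking. Coma score, CT class, optic nerve sheath cutoff, Doppler and time from trauma also restrict who can enter. The room for steering is limited, though not nil.
- **The 75% is a worst case.** It assumes that all past arms are known, which is not the planned state of a blinded trial. On the same assumption, varied blocks bring it down only to about 69%. This stands: the gain lies in removing certainty.
- **Who holds the list** is a detail that a condensed article may leave to the full protocol. Its absence is no finding.

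**Conclusion.** The point holds as a design vulnerability. With a fixed, published block of 2 on a single list, half of all allocations (16 of 32) are certain given earlier ones, and any one unblinding gives the paired patient's arm with certainty to a person who knows enrolment order. With every past arm known, guesses would be right 75% of the time. No breach of concealment or of assessor blinding is shown, and no size of bias can be put on the primary result.

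The conclusion assumes one unstratified list, enrolment order visible at the site, and at least one arm becoming known. The first two are natural readings of the article. The third is made plausible by the wording on unblinding but is not demonstrated.

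**What to change.** 1. Complete any half-filled pair from the current list. Then, by documented amendment, allocate the remaining patients from a new list with randomly varying block sizes, for example 4 and 6, and leave the sizes out of anything that site staff or the public can read. The gain applies only to patients not yet randomised; the 6% in the table is for a full list of 32.
2. Remove dropout as a stand-alone ground for unblinding, and replace the open ending of that list with stated grounds. This also protects GOSE assessments still to come, even if enrolment is far advanced.
3. State whether the treating therapist is blinded.

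**Cost.** The amendment itself and a new list. The arms may differ by up to 3 if recruitment stops halfway through a block of 6. If exactly 32 are randomised after completed pairs, the last block can only be cut at an even position, so the worst split is 17 to 15. The 30 versus 32 inconsistency has to be settled separately before the length of the new list is set. Sample size and analysis do not change.
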